### Tertiary Analysis

We will attempt to build a machine learning model to predict depression, stress, or well-being based on single modalities. Various methods, such as support vector machine, decision tree, and deep learning, are used for the machine learning analysis. Machine learning algorithms that estimate stress, well-being, and degree of depression are generated from each of these vital data sets. We will attempt to build a model not only for single modalities, but also one that can utilize all the modalities, namely pulse wave data, voice data, electrodermal activity data, body motion data, and body temperature data, together.

### Sample Size

Based on the data obtained from the pilot study (28 cases) conducted prior to this study, we estimated the PSS scores using machine learning analysis of pulse wave and speech data. A gradient boosting decision tree was used for the machine learning algorithm, and hyper parameter was adapted by random search. Accuracy verification is based on 3-fold cross validation. In order to examine the accuracy for each data size, an arbitrary number of data points were extracted at random, and the accuracy for the data size was calculated. The pilot study sample size of 28 subjects was divided and incremented for prediction. The error in the PSS score range of 0–40 corresponds to a score of 2 when an error in the predicted value of PSS of up to around 5% is warranted. When aiming for a root mean square error of 2 or less, we found that 200 cases are required, as shown in Figure 1. Regarding dropouts, we considered that the 4-week-long observation as well as filling out multiple self-rating scales can be burdensome to participants, and the dropout rate can be high. Considering the dropout rate would be 30–35%, we will aim to recruit 300 cases.

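### The 200 cases said to give a PSS RMSE of 2 or less are not supported by a learning curve over data points from 28 pilot participants

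*Protocol article*

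**What the plan says.** All of this is in the Sample Size section of the protocol article.

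- The source is the pilot: "Based on the data obtained from the pilot study (28 cases) conducted prior to this study".
- The model predicted the PSS from pulse wave and speech features: "A gradient boosting decision tree was used for the machine learning algorithm, and hyper parameter was adapted by random search". On validation the section says: "Accuracy verification is based on 3-fold cross validation".
- The curve was built by subsampling: "an arbitrary number of data points were extracted at random, and the accuracy for the data size was calculated". The next sentence is "The pilot study sample size of 28 subjects was divided and incremented for prediction".
- The accuracy target is 5% of the PSS range: "The error in the PSS score range of 0–40 corresponds to a score of 2".
- The conclusion is "When aiming for a root mean square error of 2 or less, we found that 200 cases are required, as shown in Figure 1".

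The section then allows for 30–35% dropout and sets recruitment at 300. The caption of Figure 1 says that the curve comes from the pilot. The figure itself was not available for this review.

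**The concern.** The section uses three units: data points, subjects and cases. The pilot is described both as 28 cases and as 28 subjects, and the recruitment target of 300 is also in cases, so a case is a person. The curve, however, was made by drawing data points. Nothing in the text connects a number of data points to a number of people, or says how a curve from 28 people reaches 200.

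This matters because it is the only sample size rationale in the article, and the 300 follows directly from the 200. The study aims at a technique for quantifying stress in office workers (Research Objectives; Discussion), so the relevant accuracy is that in people whom the model has not seen. More data points from the same 28 people do not show how that accuracy improves as people are added.

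**Working it through.** **Inputs from the Sample Size section:** pilot 28 people; 3-fold cross-validation; PSS range 0–40; tolerated error 5%; required number 200; dropout 30–35%; recruitment 300. The article gives no PSS standard deviation, no number of records or PSS assessments per pilot participant, and no values from the curve.

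**Steps that reproduce**

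1. Target: 0.05 × 40 = 2 PSS points.
2. Dropout, as 200/(1 − d): 200/0.70 = 286; 200/(2/3) = 300; 200/0.65 = 308. Conversely, 300 recruits leave 300 × 0.65 = 195 to 300 × 0.70 = 210 completers. The 300 follows from the 200.

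**The step that does not reproduce: the 200**

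3. 200/28 = 7.1. If the horizontal axis counts data points, 200 is about 7 per person. If it counts people, 200 is 7.1 times the largest size the pilot could have reached.
4. With three folds, each model trains on the data of about 28 × 2/3 ≈ 19 people and tests on about 28/3 ≈ 9, if folds are split by person. No arrangement of 28 people yields an observed error for a model trained on more than 28.

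**How demanding the target is (assumed SDs)**

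5. The R² needed in new people is 1 − 2²/SD². For a PSS SD of 5, 6 or 7 this is 0.84, 0.89 or 0.92.

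**What fold splitting could do (illustration only)**

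6. Data were simulated for 28 people whose features identify the person but carry no information on the PSS. Each person has one PSS value.

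| Learner and assumptions | Folds split by data point, RMSE at 200 points | Folds split by person, RMSE |
|---|---|---|
| Gradient boosting, SD 6, 20 features, ICC 0.60 | 4.58 | 7.04 |
| same, ICC 0.80 | 3.18 | 6.47 |
| same, ICC 0.95 | 1.99 | 6.59 |
| Nearest neighbour, 10 features, SD 5 / 6 / 7 | 1.10 / 1.14 / 1.38 | about 7.0 / 8.2 / 9.5 |

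The gradient boosting rows average 15 replicates per cell and the nearest-neighbour row 60. Split by data point, the nearest-neighbour RMSE falls from 5.0 / 5.8 / 6.5 at 28 points to 2.3 / 2.8 / 3.3 at 100. Split by person, it hardly changes with the number of points. A falling curve can therefore arise from recognising people already in the training data. How far it falls depends heavily on the assumptions.

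**Precision that a given number of people offers**

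7. The 95% interval for an RMSE is RMSE × √(n/χ²), with the upper and lower 2.5% points of χ² on n degrees of freedom. Around an RMSE of 2, n = 200 gives 1.82 to 2.22 (−9% to +11%), and n = 28 gives 1.59 to 2.70 (−21% to +35%). This assumes independent, normal prediction errors from a fixed model. The value 2 is only a scale; the percentages do not depend on it.

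**The case against.** The best defence has four parts.

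- **Figure 1 is not visible.** It may show the axis unit, a fitted curve and an error band. That stands as a limit, so an absent curve or interval in the figure cannot be criticised. It does not rescue the text, which reports the 200 as found from a 28-person pilot and mentions neither extrapolation nor a conversion between units.
- **Fold assignment and nested tuning are details that an article may leave to the full protocol.** This also stands. A reader might infer that the same person's data sat in both training and test folds, or that tuning and scoring on the same 28 people made the RMSE too low. The article does not say how folds were formed or whether tuning was nested, so neither is established. Both are conditional risks. In the simulation with gradient boosting, the pilot's own type of learner, leakage alone reaches 2 at 200 points only at an ICC of 0.95.
- **RMSE ≤2 is an aim in an exploratory, single-arm observational study.** No hypothesis test or error rate rests on it. This limits the consequences, but the section still says that 200 cases are required for that aim.
- **The number may be adequate anyway.** It may be. The point concerns the stated basis, and the target and dropout steps are sound.

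**Conclusion.** The point holds in a limited form. The 200 is either a count of data points relabelled as people or an unacknowledged extrapolation to 7.1 times the pilot size. In both cases the claim that 200 people give a PSS RMSE of 2 or less in new workers is unsupported. This needs only the 28, the 200 and the units used in the text; it does not depend on the simulations.

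A reader might go further and conclude that 200 is too small, or that the study will miss its accuracy target by a wide margin. The documents do not support that. Without the PSS SD, the records per person and the curve values, no corrected number can be derived, and the simulations show what could happen under an assumed SD, ICC, feature count and absence of signal, not what happened in the pilot.

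**What to change.** 1. State what the horizontal axis of Figure 1 counts.
2. Rerun the learning curve on the existing pilot data with number of participants on the horizontal axis, all of a person's data in one fold, and the hyperparameter search nested within the training folds.
3. Mark any part of the curve beyond 28 participants as extrapolation, name the fitted form and show its uncertainty.
4. If RMSE ≤2 at 200 people is not supported, withdraw that claim. Keep 200 completers (300 recruited) as a feasibility size and give its precision: about ±10% relative on the RMSE, assuming independent, approximately normal prediction errors. Cross-validated errors from one pooled sample are not strictly independent, so this figure is a rough guide.

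Possible wording if the claim is withdrawn: *The target of 200 completers was set on grounds of feasibility. If prediction errors are independent and approximately normal, it estimates the RMSE for the PSS to within about 10%. The pilot of 28 participants does not establish the RMSE to be expected at this size.*

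The cost is a small re-analysis of data already held, a rewritten paragraph and probably a less favourable stated accuracy. Recruitment stays at 300.

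### A target of 300 keeps the required 200 only up to one-third dropout; at the stated upper limit of 35% it leaves 195

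*Protocol article*

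**What the plan says.** Everything needed is in the Sample Size section of the protocol article.

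- The required number comes from a learning-curve exercise on a 28-case pilot that predicted the PSS score from pulse wave and speech data: "When aiming for a root mean square error of 2 or less, we found that 200 cases are required".
- The accuracy target is tied to the scale: "The error in the PSS score range of 0–40 corresponds to a score of 2", on the basis that an error of around 5% is acceptable.
- The section expects substantial loss because of the four-week observation and the questionnaires: "filling out multiple self-rating scales can be burdensome to participants, and the dropout rate can be high".
- It then combines the two: "Considering the dropout rate would be 30–35%, we will aim to recruit 300 cases".

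The section does not say which point in the 30–35% range the 300 was calculated for. No other section of the article gives a different target or dropout rate.

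**The concern.** When a protocol gives a required number, a range for the expected loss and a recruitment target meant to absorb that loss, a reader takes the target to hold across the range. Here it holds over most of the range but not at the top. The upper limit is not presented as a remote possibility: it is part of the planning assumption, and the same section says dropout may be high.

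What is at stake is how the sample-size statement reads. If dropout came in at 35%, as the protocol allows, the study would finish with fewer cases than the number it calls required, although it had met its recruitment target and stayed within its own assumption. The text should say what 300 does and does not cover.

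**Working it through.** **Inputs** (all from Sample Size, protocol article)

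- Required cases: n = 200
- Anticipated dropout: d = 30% to 35%
- Recruitment target: N = 300

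**Step 1. Reproduce the 300.** The number to recruit is N = n / (1 − d), rounded up.

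| Dropout d | 200 / (1 − d) | Recruits needed |
|---|---|---|
| 30% | 200 / 0.70 = 285.7 | 286 |
| 32.5% (midpoint) | 200 / 0.675 = 296.3 | 297 |
| 33.3% (one third) | 200 / 0.667 = 300 | 300 |
| 35% | 200 / 0.65 = 307.7 | 308 |

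The stated 300 is reproduced exactly at a dropout of one third, which lies inside the range. The usual mistake, multiplying by (1 + d), would give 200 × 1.30 = 260 to 200 × 1.35 = 270, so it does not explain the 300. The inflation method is sound.

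**Step 2. Work forward from 300.** The number retained is 300 × (1 − d).

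| Dropout d | Retained | Against 200 |
|---|---|---|
| 30% | 300 × 0.70 = 210 | +10 |
| 32.5% | 300 × 0.675 = 202.5 | +2.5 |
| 33.3% | 300 × 0.667 = 200 | 0 |
| 35% | 300 × 0.65 = 195 | −5 |

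**Step 3. Find the break-even.** Setting 300 × (1 − d) = 200 gives d = 1 − 200/300 = 33.3%. The uncovered part of the range runs from 33.3% to 35%. That is about 1.7 percentage points of a 5-point range, or its upper third.

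**Step 4. Size of the gap at 35%.** In retained cases: 200 − 195 = 5, and 5/200 = 2.5%. In recruits: 308 − 300 = 8, and 8/300 = 2.7%.

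**What cannot be computed.** The 200 was read from the pilot curve in Figure 1, which is not shown. The RMSE expected at 195 cases, and the difference from that at 200, therefore cannot be derived.

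**The case against.** The strongest reply is that nothing has been miscalculated. The section gives a loose range and a round target, and it does not promise 200 cases at the worst end. The target covers the midpoint with a little to spare and is exact at one third. Planning for the upper limit is good practice, but the text did not commit to it. The requirement is itself a round figure taken from a 28-case pilot with a tolerance of about 5%, and such a figure can hardly separate 195 from 200.

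Most of this stands, and it keeps the point small. It does not remove it: the protocol calls 200 required, names 35% as part of what it expects, and does not say that 300 was set for a lower rate.

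A reader might infer three stronger things, none of which the document supports.

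- *That the accuracy target would be missed at 35% dropout.* Only the case number stated for that target would be missed. The effect on RMSE is unknown without Figure 1.
- *That the 30–35% covers only people who leave the study, so that participants lacking one sensor stream are a further loss.* The section does not define dropout. It justifies the rate partly by the burden of the questionnaires, so incomplete data may already be included. The Discussion treats missed questionnaires and missing biometric data as an adherence issue and describes steps to limit it.
- *That the model using all modalities would fall further below 200.* The 200 was derived for pulse wave and speech data only. The all-modality model has no stated size or accuracy target, and the document gives no rate of sensor loss from which to calculate one.

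**Conclusion.** The point holds as a minor inconsistency within the Sample Size section. Three stated numbers (200 required, up to 35% dropout, 300 recruited) do not fit together at the top of the dropout range, where 195 cases remain. The shortfall is 5 cases, and it arises only if dropout exceeds 33.3%.

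This rests on two readings: that the 200 are cases remaining after dropout, which is the only reading under which inflating to 300 makes sense, and that the dropout rate applies to all those recruited. It does not show that the 300 is wrong, that the inflation formula was misapplied, or that the study would fail to reach its accuracy target.

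**What to change.** Replace the last sentence of the Sample Size section with wording such as:

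> Recruiting 300 allows for dropout of up to 33% (200 retained); at 35% dropout about 195 would remain.

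This costs one sentence. It needs no extra recruitment and no change to design or analysis. The only downside is that the stated dropout allowance looks slightly less favourable than the present text suggests. If the sponsor would rather keep 200 cases across the full range, the matching target is 308, which is 8 more recruits, but a gap of this size does not call for that.

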**Figure 1 F1:**
[figure not shown]
Sample size and root mean square error of the PSS score in the pilot study.

## Discussion

The main aim of this study is to develop a technique to quantify stress and well-being in a way that does not disturb the workplace using vital data. Depression is a major problem in the field of occupational health, with its high incidence, especially among people of working age. The social significance of our project will be great because the occurrence of psychiatric disorders such as depression may be suppressed through self-management and improvement of working conditions in the companies if the quantitative measurement of stress and well-being, which is the ultimate goal of this study, can be achieved.

In this study, biometric information such as pulse wave, voice, and skin potential will be collected without any special intervention while the research collaborators are working. In addition, the research collaborators will be asked to cooperate in data entry through questionnaires, but as described below, the burden will be kept to a certain extent. We will use a web camera, a microphone, a wrist-band wearable device to obtain pulse, voice, and skin potential data, and a web-based questionnaire, which may cause psychological, physical, and time burdens. However, we believe that the burden will be small because we will not intervene and the questionnaire will be administered in a way that will not interfere with normal work and it takes a maximum of about 10 min per session.

The study will also include a rating scale for depression, on which significantly higher scores are presumed to indicate a higher risk of depression. If a recruited person will present any psychiatric disorder during the study, he or she will receive information that would not have been available to him or her if he or she had not participated in the study. The possibility that this may lead to a psychological burden on the individual cannot be denied. Only individuals who agreed that he or she will be informed of accidental findings are recruited. In addition, when the score of the rating scale for depression indicates he or she may have depression, an appropriate action should be taken, such as referring the participant to an appropriate medical institution if he or she wishes to do so. Moreover, the participant will be informed that sensing can be discontinued by shutting down the software or removing the wearable device, and that he or she may do so temporarily if it causes a psychological burden. Prior to the study, consent with the field companies will be obtained using a memorandum of understanding to ensure the privacy of research collaborators (e.g., not to disclose data without the participant's consent).

Challenges of the study are as follows. First, there will be a potential bias that those who are originally interested in the physical and mental health conditions may collaborate in the study. For this reason, participants who are currently being treated for psychiatric disorders, such as depression, will be excluded from the study, and efforts will be made to recruit a wide range of participants. Second, there will be also the issue of adherence. Failure to fill out the questionnaire or not obtaining biometric data may be considered. The researchers will try to reduce the burden on research participants as much as possible to minimize the time and effort required for inputting information and improve adherence. The researchers also consider rewarding each participant based on the response rate to the survey and the amount of time the participant will spend using the devices. Third, as the data collection is done in a natural setting in workplaces, we will lack the control data such as setting participants an experimental task where we can compare the data under strong stress.

## Ethics Statement

Our study has received approval from the institutional review board at Keio University School of Medicine. Approval was granted on April 22, 2019. This study is registered in the University Hospital Medical Information Network (UMIN) (UMIN000036814). Participants' inclusion will be voluntary. Written consent will be obtained from every participant. Participants will be free to withdraw from the study at any time.
